**10. REQUIRED DATA**

| Cycle                                                                               | Screen
* | Cycle 1        |                |                |                | Cycle 2 |   |   |   | Subsequent Cycles
*** |   | Study Withdrawal |
|-------------------------------------------------------------------------------------|-------------|----------------|----------------|----------------|----------------|---------|---|---|---|--------------------------|---|------------------|
| Week                                                                                | 0           | 1              | 2              | 3              | 4              | 1       | 2 | 3 | 4 | 1                        | 3 |                  |
| Informed consent                                                                    | X           |                |                |                |                |         |   |   |   |                          |   |                  |
| Medical history                                                                     | X           |                |                |                |                |         |   |   |   |                          |   |                  |
| Previous treatments
(specific surgery,
radiation, chemo)                      | X           |                |                |                |                |         |   |   |   |                          |   |                  |
| Inclusion/exclusion
criteria                                                     | X           |                |                |                |                |         |   |   |   |                          |   |                  |
| Collect Tumor Blocks A                                                   | X           |                |                |                |                |         |   |   |   |                          |   |                  |
| Physical examination                                                                | X           | X              | X              | X              |                | X       |   | X |   | X                        | X | X                |
| Vital signs                                                                         | X           | X              | X              | X              | X              | X       | X | X | X | X                        | X |                  |
| EKG                                                                                 | X †         | X ‡            | X              |                | X              |         |   |   | X | C                        |   | X                |
| CBC with differential                                                               | X           |                |                | X              |                | X       |   | X |   | X                        | X | X                |
| Electrolytes (including
K+, Ca++ and Mg++),
creatinine, BUN, LFTs             | X           |                | X              | X              | X              | X       | X | X | X | X                        | X |                  |
| Urinalysis                                                                          | X           |                |                |                |                | X       |   |   |   | X                        |   |                  |
| Pregnancy test **                                                                   | X           |                |                |                |                |         |   |   |   |                          |   |                  |
| Performance Status                                                                  | X           | X              |                | X              |                | X       |   | X |   | X                        | X | X                |
| Imaging for RECIST
measurements                                                  | X           |                |                |                |                |         |   |   |   | X                        |   | X                |
| Blood samples –
plasma VEGF and
circulating endothelial
cells V |             | X V | X V | X V | X V |         |   |   |   | X V           |   |                  |
| Tolerability/AE
reporting                                                        | X           | X              | X              | X              |                | X       |   | X |   | X                        | X | X                |
| Assessment of
Concomitant
medication                                          | X           | X              |                |                |                |         |   |   |   | X                        |   |                  |

\* within 4 wks prior to 1st dose of therapy, except lab work which must be within 7 working days prior to 1st dose of therapy.

\*\* Females only; women who are documented to be postmenopausal for > 1 year or s/p hysterectomy do not need testing. Urine or serum

\*\*\* Lab work not needed on cetuximab-only days during subsequent cycles

† The screening QTc must be <480 msec or ≤460msec if patient is taking drugs known to cause Torsades de Pointes (Appendix A; Drug List 1, section 5.2) Up to 3 ECGs **may** be obtained at screening, and the mean QTc value used to determine eligibility.

‡ Within 3 days of or on C1 D1, “baseline” 12-lead ECGs are to be performed pre-dose. Baseline QTc will be determined by the average of no less than 3 consecutive ECGs (within 5-10 minutes of one another). Patients who are receiving drugs that may induce Torsades de Pointes must have an additional ECG obtained 4-8 hours after the first dose of ZD6474.

C After cycle 2, EKG required at week 12 (cycle 3, week 4)

A To be obtained from all patients on study – block does not need to arrive prior to starting therapy – only request to pathology made.

V See Appendix C – only for patients treated at MTD. Pre-treatment on cycle 1, day 1 and anytime on cycle 1, days 8, 15 and 22 and on day 1 of each subsequent cycle.

## 11 PATIENT WITHDRAWAL AND STUDY TERMINATION

Patients may withdraw from the trial at any time and for any reason. Some possible reasons for early withdrawal include the following:

- Disease progression
- Development of an intercurrent medical condition or need for concomitant treatment that precludes further participation in the trial
- Unacceptable toxicity or any adverse event (as outlined in section 7) that precludes further participation in the trial
- The investigator removes the patient from the trial in the best interests of the patient
- Inability of subject to comply with study requirements
- Determination by the investigator that it is no longer safe for the subject to continue therapy
- Study completion or discontinuation
- Patient withdraws consent to continued participation in the trial
- Interruption of treatment beyond allowed based on section 7

The reason and date of discontinuation are to be documented in the patient's medical record and in the CRF.

The investigator should complete all end of treatment procedures when a patient withdraws from treatment. All patients who discontinue the trial secondary to an adverse event should be followed until resolution, stabilization or return to a baseline condition.

**ALL PATIENTS WHO RECEIVE ONE DOSE OF TREATMENT SHOULD BE INCLUDED IN ANY SAFETY ANALYSIS.**

**THE INVESTIGATOR MAY DISCONTINUE THE TRIAL AT ANY TIME. REASONS FOR EARLY TRIAL DISCONTINUATION MAY INCLUDE, BUT ARE NOT LIMITED TO, UNACCEPTABLE TOXICITY OF STUDY TREATMENT, A REQUEST TO DISCONTINUE THE TRIAL FROM A REGULATORY AUTHORITY OR AN IRB, OR POOR ENROLLMENT.**

## 12 MEASUREMENT OF EFFECT

Response and progression will be evaluated in this study using the new international criteria proposed by the Response Evaluation Criteria in Solid Tumors (RECIST) Committee. Changes in only the largest diameter (unidimensional measurement) of the tumor lesions are used in the RECIST criteria. Note: Lesions are either measurable or non-measurable using the criteria provided below. The term

“evaluable” in reference to measurability will not be used because it does not provide additional meaning or accuracy.

## 12.1 Eligibility

Though the primary endpoint is determination of an MTD, the secondary endpoint of efficacy is very important in this study and patients must have measurable disease by RECIST.

**Measurable disease** - the presence of at least one measurable lesion. If the measurable disease is restricted to a solitary lesion, its neoplastic nature should be confirmed by cytology/histology.

**Measurable lesions** - lesions that can be accurately measured in at least one dimension with longest diameter  $\geq 20$  mm using conventional techniques or  $\geq 10$  mm with spiral CT scan.

**Non-measurable lesions** - all other lesions, including small lesions (longest diameter  $< 20$  mm with conventional techniques or  $< 10$  mm with spiral CT scan), i.e., bone lesions, leptomeningeal disease, ascites, pleural/pericardial effusion, inflammatory breast disease, lymphangitis cutis/pulmonis, cystic lesions, and also abdominal masses that are not confirmed and followed by imaging techniques.

All measurements should be taken and recorded in metric notation, using a ruler or calipers. All baseline evaluations should be performed as closely as possible to the beginning of treatment and never more than 4 weeks before the beginning of the treatment.

The same method of assessment and the same technique should be used to characterize each identified and reported lesion at baseline and during follow-up. Clinical lesions will only be considered measurable when they are superficial (e.g., skin nodules and palpable lymph nodes). For the case of skin lesions, documentation by color photography, including a ruler to estimate the size of the lesion, is recommended.

## 12.2 Methods of Measurement

CT and MRI are the best currently available and reproducible methods to measure target lesions selected for response assessment. The utilization of endoscopy and laparoscopy for objective tumor evaluation has not yet been fully and widely validated. Their uses in this specific context require sophisticated equipment and a high level of expertise that may only be available in some centers. Therefore, the utilization of such techniques for objective tumor response should be restricted to validation purposes in specialized centers. However, such techniques can be useful in confirming complete pathological response when biopsies are obtained.

Tumor markers alone cannot be used to assess response. If markers are initially above the upper normal limit, they must normalize for a patient to be considered in complete clinical response when all lesions have disappeared.

Cytology and histology can be used to differentiate between PR and CR in rare cases (e.g., after treatment to differentiate between residual benign lesions and residual malignant lesions in tumor types such as germ cell tumors).

### 12.3 Baseline documentation of "Target" and "Non-Target" lesions

All measurable lesions up to a maximum of five lesions per organ and 10 lesions in total, representative of all involved organs should be identified as **target lesions** and recorded and measured at baseline.

Target lesions should be selected on the basis of their size (lesions with the longest diameter) and their suitability for accurate repeated measurements (either by imaging techniques or clinically).

A sum of the longest diameter (LD) for *all target lesions* will be calculated and reported as the baseline sum LD. The baseline sum LD will be used as reference by which to characterize the objective tumor.

All other lesions (or sites of disease) should be identified as **non-target lesions** and should also be recorded at baseline. Measurements of these lesions are not required, but the presence or absence of each should be noted throughout follow-up.

### 12.4 Response Criteria

#### Evaluation of target lesions

- \* Complete Response (CR): Disappearance of all target lesions
- \* Partial Response (PR): At least a 30% decrease in the sum of the LD of target lesions, taking as reference the baseline sum LD
- \* Progressive Disease (PD): At least a 20% increase in the sum of the LD of target lesions, taking as reference the smallest sum LD recorded since the treatment started or the appearance of one or more new lesions
- \* Stable Disease (SD): Neither sufficient shrinkage to qualify for PR nor sufficient increase to qualify for PD, taking as reference the smallest sum LD since the treatment started

#### Evaluation of non-target lesions

- \* Complete Response (CR): Disappearance of all non-target lesions and normalization of tumor marker level
- \* Incomplete Response/  
Stable Disease (SD): Persistence of one or more non-target lesion(s) or/and maintenance of tumor marker level above the normal limits
- \* Progressive Disease (PD): Appearance of one or more new lesions and/or unequivocal progression of existing non-target lesions (1)

- (1) Although a clear progression of "non target" lesions only is exceptional, in such circumstances, the opinion of the treating physician should prevail and the progression status should be confirmed later on by the review panel (or study chair).

## 12.5 Evaluation of best overall response

The best overall response is the best response recorded from the start of the treatment until disease progression/recurrence (taking as reference for PD the smallest measurements recorded since the treatment started). In general, the patient's best response assignment will depend on the achievement of both measurement and confirmation criteria

| Target lesions | Non-Target lesions | Evaluation of non-target lesions | Overall response |
|-----------------------|---------------------------|-----------------------------------------|-------------------------|
| CR                    | CR                        | No                                      | CR                      |
| CR                    | Incomplete response/SD    | No                                      | PR                      |
| PR                    | Non-PD                    | No                                      | PR                      |
| SD                    | Non-PD                    | No                                      | SD                      |
| PD                    | Any                       | Yes or No                               | PD                      |
| Any                   | PD                        | Yes or No                               | PD                      |
| Any                   | Any                       | Yes                                     | PD                      |

Patients with a global deterioration of health status requiring discontinuation of treatment without objective evidence of disease progression at that time should be classified as having "symptomatic deterioration". Every effort should be made to document the objective progression even after discontinuation of treatment.

In some circumstances it may be difficult to distinguish residual disease from normal tissue. When the evaluation of complete response depends on this determination, it is recommended that the residual lesion be investigated (fine needle aspirate/biopsy) to confirm the complete response status.

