#### 12.8 Reporting of results

All patients included in the study must be assessed for response to treatment, even if there are major protocol treatment deviations or if they are ineligible. Each patient will be assigned one of the following categories: 1) complete response, 2) partial response, 3) stable disease, 4) progressive disease, 5) early death from malignant disease, 6) early death from toxicity, 7) early death because of other cause, or 9) unknown (not assessable, insufficient data). All conclusions should be based on all eligible patients. Since patients will be treated with differing doses, response rate will be reported in descriptive analyses. Since this is a phase I study, response rates for each dose level and the MTD will be reported and considered secondary analyses.

Exploratory subanalyses may then be performed on the basis of a subset of patients, excluding those for whom major protocol deviations have been identified (e.g., early death due to other reasons, early discontinuation of treatment, major protocol violations, etc.). However, these subanalyses may not serve as the basis for drawing conclusions concerning treatment efficacy, and the reasons for excluding patients from the analysis should be clearly reported.

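### The Yes/No column of the best-overall-response table in Section 12.5 carries the wrong heading, so the rule read literally contradicts its own second column and Section 12.3

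*Protocol*

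**What the plan says.** Section 12.5 of the protocol gives a seven-row table that turns three inputs into an overall response. The first input is the target-lesion category. The second is the non-target category, with entries such as CR, "Incomplete response/SD", Non-PD and PD. The third column is headed "Evaluation of non-target lesions" and contains only No, Yes, or either.

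Three other places bear on how that column should be read:

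- Section 12.3, on non-target lesions: "Measurements of these lesions are not required, but the presence or absence of each should be noted throughout follow-up".
- Section 12.4, target-lesion criteria: progressive disease includes "or the appearance of one or more new lesions".
- Section 12.4, non-target criteria: progressive disease is "Appearance of one or more new lesions and/or unequivocal progression of existing non-target lesions".

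Section 12.8 gives the status of the endpoint that the table feeds: "response rates for each dose level and the MTD will be reported and considered secondary analyses".

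**The concern.** A Yes/No entry under that heading says whether non-target lesions were assessed, not what the assessment showed. The non-target finding already has its own column. As worded, the rule therefore makes part of the response category depend on whether an examination took place.

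This table is the protocol's only rule for combining target and non-target findings into one overall response. If it cannot be applied as printed, each assessor must work out for themselves what the third column means before a best overall response can be assigned. Section 12.1 describes efficacy as very important in this study, and three centers are expected, so the rule should be readable without inference.

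**Working it through.** No arithmetic is involved. The check reads each row twice, first with the heading as printed and then with the third column taken as new lesions, and compares both readings with Sections 12.3 and 12.4.

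| Row | Target | Non-target | Third column | Overall | Heading as printed | Third column as new lesions |
|---|---|---|---|---|---|---|
| 1 | CR | CR | No | CR | Non-target result given, yet not evaluated | Coherent |
| 2 | CR | Incomplete/SD | No | PR | Same contradiction | Coherent |
| 3 | PR | Non-PD | No | PR | Same, for any patient with non-target lesions | Coherent |
| 4 | SD | Non-PD | No | SD | Same, for any patient with non-target lesions | Coherent |
| 5 | PD | Any | Either | PD | Third column has no influence | Coherent |
| 6 | Any | PD | Either | PD | Third column has no influence | Coherent |
| 7 | Any | Any | Yes | PD | PD because an evaluation was done | Coherent: a new lesion is PD |

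**Step 1: the table against itself.** Rows 1 and 2 need a non-target status that can only come from looking at the non-target lesions, while the third column says that this was not done. Rows 3 and 4 have the same conflict for a patient with non-target disease. Row 7 returns progression from the fact of evaluation alone.

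**Step 2: the table against Section 12.3.** Non-target lesions must be followed throughout, so Yes is the expected entry for every patient who has them. Rows 1 to 4 are then closed to such a patient, and row 7 applies whatever the lesions show.

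**Step 3: what the column was meant to hold.** If the third column is read as new lesions, all seven rows are coherent. CR, PR and SD require that none has appeared, and a new lesion gives PD whatever the other two columns show. That agrees with both definitions of progression in Section 12.4.

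**Step 4: whether new lesions are lost as printed.** They are not. Under Section 12.4 target-lesion progression is judged by "taking as reference the smallest sum LD recorded since the treatment started or the appearance of one or more new lesions", so a new lesion makes the first column PD. The non-target criteria do the same for the second column. Rows 5 and 6 then return PD with either entry in the third column.

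**Result.** Five of the seven rows (1 to 4 and 7) are affected by the heading. The two rows that carry a new lesion through from Section 12.4 are not.

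**The case against.** The strongest reply is that nobody would apply the printed heading. Section 12 states that RECIST is used, Section 12.4 sets out the criteria correctly just above the table, and the contradiction in rows 1 and 2 tells an assessor that the literal reading is unusable. This stands as a limit on the practical effect. It does not make the heading right, because the reader still has to correct the table in order to use it.

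A second reply is that the heading may be an artefact of reading the PDF by program, since it repeats word for word the sub-heading of the non-target criteria in Section 12.4. This cannot be excluded without the source page. It is unlikely, because the heading is complete and the table is otherwise well formed.

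Three stronger inferences are tempting, and the documents do not support them:

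- *New lesions play no part in the table, so a responder with a new lesion would keep the response.* Section 12.4 classes that patient as PD in both of the first two columns, and rows 5 and 6 return PD.
- *Patients with non-target disease would in practice be scored as progressors, which would cap the response rate.* That needs a reading that assessors could not apply consistently, and a prevalence of non-target disease that the protocol does not give.
- *Progression-free survival, the end of treatment or the case report form are also affected.* Progression is defined in Section 12.4. Section 3.5 ends treatment at disease progression, and Section 12.7 ends response duration at objectively documented progression, neither by reference to this table. No response form is among the documents.

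**Conclusion.** The point holds as a mislabelled column. The third heading in the Section 12.5 table does not fit its entries, duplicates the subject of the second column, and read literally conflicts with Section 12.3. New lesions lack a labelled column but still lead to PD through Section 12.4.

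The effect is limited to the assignment of best overall response. That feeds a secondary endpoint reported descriptively by dose level and at the maximum tolerated dose. The primary objective rests on dose-limiting toxicities and is not touched. No numerical effect on the response rate can be derived from the documents.

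The conclusion assumes that the heading on the source page matches the text as read. That the column was meant for new lesions is an inference from its Yes/No pattern and from Section 12.4. It is the reading under which every row works.

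**What to change.** Check the heading against the source page of the protocol. If it reads as shown, rename the third column of the Section 12.5 table *New lesions* (Yes/No) and leave all seven rows unchanged. The table then agrees with Section 12.4 and no longer conflicts with Section 12.3.

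The cost is one column heading in the protocol text. No additional data, assessments or analyses are needed.
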